#### Acceptability

In the 6-month follow-up survey, participants completed questions regarding their overall level of satisfaction with the intervention (*In general how satisfied were you with the intervention?*); their satisfaction with each component of the intervention; the degree to which these components were accessed, read, and/or used; and how helpful they were. We also conducted a poststudy qualitative interview with the study participants to explore how they found out about the study and why they joined, their perceptions about various study protocols (recruitment, visits, treadmill walk, incentives, etc) and individual components of the intervention (eg, website components, text messages, Facebook, and gym membership), and thoughts on ideas for future interventions. Qualitative interviews were digitally recorded, with the recordings sent to a professional company for transcription and translation into English. The transcribed responses to each interview question are being thematically coded by graduate students using similar methods as the focus groups described above.

#### Power Analysis

Our sample size estimates were based on results from 2 of our completed studies with accelerometer data for Latina participants [12,15]. In addition, in a small pilot [19], the mean change from baseline to 6 months in MVPA from the subsample of male participants who were given accelerometers was 76.4 min per week (SD 113.5) for the intervention versus 15.0 min (SD 22.6) for the control. Although the effect size (*d*=0.75) was large, the subsample was small (N=9) and, thus, must be considered with caution. In our recently completed intervention with Latinas [15], the mean change in total MVPA was 42.5 min per week (SD 81.8) for the intervention versus 9.0 min (SD 45.7) for the control, yielding an effect size of *d*=0.51. With 25 participants randomized to each arm, we expected to have at least 43% power to detect differences in accelerometer-measured MVPA between conditions at 6 months, assuming an effect size of *d*=0.51 and 75% power if *d*=0.75, using a two-tailed significance α of .05. The web-based program for Latinas had a slightly higher effect size; therefore, this was a conservative estimate. Although we do not expect to achieve statistically significant group differences in this pilot study, we will determine the effect size achieved between groups and use these data to estimate the sample size needs for a future RCT.

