### Objectives

The purpose of this protocol paper is to describe the study design, intervention, and evaluation methods for Hombres Saludables, an internet- and text-based tailored Spanish language intervention designed for an ethnically diverse population of Latino men (ie, Caribbean and Central and South American origin) to increase total PA. This intervention was adapted from our culturally and linguistically appropriate, internet-based PA intervention for Latina women, Pasos Hacia la Salud [14], which successfully increased and maintained total PA levels in Latina women over 12 months [15,37].

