## Methods

### Overall Design

Hombres Saludables is a 6-month randomized controlled trial (RCT) for Latino men comparing an individually tailored, internet- and text-based PA intervention with a control group that received an attention-matched intervention about nutrition and wellness. The primary aims of the study are to determine the feasibility, acceptability, and preliminary efficacy of the intervention, as well as the recruitment, implementation, and evaluation protocols. Secondary aims include examining potential moderators (eg, demographics, acculturation, and environmental variables such as the neighborhood and socioeconomic environments) and mediators (eg, self-efficacy and cognitive and behavioral processes of change) of treatment effects at 6 months post randomization. The targeted sample size for this pilot trial is 50 Latino men.

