#### Planned Analyses

The primary aim of this study is to determine the feasibility, acceptability, and preliminary efficacy of the tailored PA intervention. We will consider the intervention feasible if at least 80% of the randomized participants are retained at the 6-month follow-up. The intervention will be considered acceptable if at least 80% of participants completing the 6-month follow-up respond favorably (*satisfied* or *very satisfied*) to the question *In general how satisfied were you with the intervention?* on the 6-month follow-up survey. We also asked more questions about intervention and study acceptability on the 6-month survey and the poststudy qualitative interviews described earlier. The main efficacy outcome was minutes per week of total MVPA, as measured by accelerometer data and PAR self-report, assessed at baseline and 6 months after baseline. The hypothesis is that participants in the PA intervention condition will have greater increases in minutes of total MVPA from baseline to post intervention (6 months) than participants in the control condition.

As a preliminary step, we will assess potential between-group differences in baseline characteristics (demographics and baseline PA level) using graphical methods and nonparametric and parametric tests as appropriate (eg, the Wilcoxon rank sum test for skewed data, *t* tests for normally distributed continuous data, and chi-square tests for categorical data). Any variables not balanced by randomization will be controlled for as covariates in subsequent analyses if they are correlated with the outcome (eg, minutes per week of MVPA) at a modest *P*<.10 level. We will estimate the preliminary efficacy of intervention compared with control using a generalized linear model in which we regress minutes per week of objectively measured MVPA at 6 months on the treatment assigned, baseline value of the outcome, and potential confounders (including those variables not balanced by randomization). To avoid the effects of outliers, we apply a normalizing transformation (if necessary) to the outcome before analysis. Should this transformation not adequately bring the data toward normality, we will model the median outcome (instead of the mean) using a quantile regression model.

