## Results

This study was funded in September 2016. Initial institutional review board approval was received in February 2017. Focus groups and intervention development were conducted from April 2017 to January 2017. Recruitment for the clinical trial was carried out from February 2018 to July 2019. Baseline data collection was carried out from February 2018 to October 2019, with a total of 43 participants randomized. Follow-up data were collected through April 2020. Data cleaning and analysis are ongoing, and we expect study results to be published in summer 2021.

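### The stated power of at least 43% (d = 0.51) and 75% (d = 0.75) treats the 25 men randomized per arm as 25 analysed; *at least* and *conservative* are unsupported

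*Protocol article*

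**What the plan says.** Overall Design sets the size: "The targeted sample size for this pilot trial is 50 Latino men". Power Analysis states: "With 25 participants randomized to each arm, we expected to have at least 43% power to detect differences in accelerometer-measured MVPA between conditions". That figure is for d = 0.51; for d = 0.75 the power is put at 75%, and the test is two-sided at the 5% level. The two effect sizes come from mean changes in weekly MVPA. The value 0.51 is from a completed intervention with Latinas (reference 15), and 0.75 is from nine men in a small pilot, which the authors say needs caution. The section closes the argument with: "The web-based program for Latinas had a slightly higher effect size; therefore, this was a conservative estimate". It gives no allowance for loss to follow-up. It adds that significant group differences are not expected.

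Three other places bear on this:

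- Planned Analyses: "We will consider the intervention feasible if at least 80% of the randomized participants are retained at the 6-month follow-up".
- Results: "with a total of 43 participants randomized".
- Objectives describes the internet-based program for Latina women from which this intervention was adapted: "Pasos Hacia la Salud [14], which successfully increased and maintained total PA levels in Latina women over 12 months [15,37".

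**The concern.** Power depends on the number of men with a 6-month outcome, not on the number randomized. The power statement is tied to the number randomized, and the words *at least* present the result as a floor. The same article would call the trial feasible with one man in five lost, and it reports fewer men randomized than planned.

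The conservative sentence adds a second assurance. It says the web-based program for Latinas had a larger effect than the one assumed, but the assumed effect is itself cited to that program.

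At stake is how firmly a reader takes 43% and 75%, both when reading the pilot's group comparison and when its data are carried into the sample size of the next trial.

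**Working it through.** **Inputs.** Power Analysis: 25 randomized per arm; two-sided α = 0.05; changes of 42.5 (SD 81.8) versus 9.0 (SD 45.7), and of 76.4 (SD 113.5) versus 15.0 (SD 22.6) min/week. Planned Analyses: retention of at least 80%; a model adjusted for the baseline value. Results: 43 randomized.

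**Step 1: effect sizes.** d = difference in mean change ÷ √[(SD₁² + SD₂²)/2].

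- Latina study: 33.5 / 66.26 = 0.506, stated as 0.51.
- Male pilot subsample: 61.4 / 81.83 = 0.750, stated as 0.75.

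Both reproduce.

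**Step 2: stated power.** The noncentrality is d / √(1/n₁ + 1/n₂). With 25 per arm it is 1.803 for d = 0.51 and 2.652 for d = 0.75.

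- Noncentral t, 48 df: 42.4% and 73.8%.
- Normal approximation: 43.8% and 75.5%.

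These bracket the stated 43% and 75%. One-sided versions do not fit (55–56% and 83–84%). The stated figures therefore use all 25 men per arm, with no loss and no baseline adjustment.

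**Step 3: same calculation at other numbers analysed.** 80% of 25 is 20 per arm. 80% of 43 is 34.4, about 17 per arm.

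| Men analysed per arm | d = 0.51, t (normal) | d = 0.75, t (normal) |
|---|---|---|
| 25 / 25: plan, no loss | 42.4% (43.8%) | 73.8% (75.5%) |
| 20 / 20: plan, 80% retained | 34.9% (36.4%) | 63.7% (66.0%) |
| 22 / 21: 43 randomized, no loss | 37.2% (38.7%) | 67.0% (69.1%) |
| 17 / 17: 43 randomized, 80% retained | 30.3% (31.8%) | 56.4% (59.0%) |

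**Step 4: what baseline adjustment could add.** The d values are on the change-score scale. Let k be the baseline SD divided by the follow-up SD, and r the baseline–follow-up correlation. Adjusting for baseline multiplies the change-score variance by (1 − r²)/(k² + 1 − 2rk). The article gives neither k nor r, so these are assumed ranges, with r from 0.2 to 0.5 and 20 per arm:

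- k = 1 (equal SDs): the factor is 0.60 at r = 0.2 and 0.75 at r = 0.5. Power is 44–53% for d = 0.51 and 76–85% for d = 0.75.
- k = 0.3 to 0.5: the factor is 0.91 to 1.00. Power is 35–38% for d = 0.51 and 64–68% for d = 0.75.

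The first case restores the stated figures at 80% retention; the second does not.

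**Step 5: the conservative sentence.** Power Analysis takes 0.51 from reference 15. Objectives cites reference 15 for the results of the internet-based program for Latina women. The sentence then says the web-based program for Latinas had a slightly higher effect than the one assumed. On these citations both sides of the comparison are the same program. No higher value is given for any study of Latinas.

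**The case against.** Several counter-arguments have force.

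- **The arithmetic is right.** Both d values and both powers reproduce at 25 per arm. This stands. The fault is an unstated assumption of complete follow-up, not a miscalculation.
- **Baseline adjustment is planned and could restore the power.** This stands as a possibility. A reader might infer that 43% and 75% are ceilings which the design cannot reach. The documents do not support that, because with equal SDs 20 per arm would meet or exceed both figures. Nor do they support the opposite assurance. One could argue for a small baseline SD from the limit of 60 min/week at entry, but that limit applies to self-reported activity, whereas the power statement concerns accelerometer data.
- **80% is a minimum success criterion, not a forecast of dropout.** Correct. The 35% and 64% describe the worst retention the plan would still call a success.
- **Randomizing 43 is trial conduct.** Correct. The power statement is in the past tense and tied to 25 per arm, and the shortfall is openly reported. It is not a planning error, and the prospective calculation should not be rewritten around it.
- **All available data are used.** This does not help here. With a single follow-up time, a man without a 6-month outcome adds essentially nothing to the treatment contrast.
- **The conservative sentence may be only a citation slip.** Power Analysis draws on two studies (references 12 and 15), and swapped citations would explain it. The article cannot settle this, so the sentence should not be read as a proven false claim.

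**Conclusion.** The point holds as a reporting fault. On the unadjusted two-group calculation that reproduces the stated figures, 43% and 75% require complete 6-month data on all 50 men. At the article's own retention threshold the same calculation gives about 35% and 64%, roughly 7 and 10 points lower by t-test than the 42.4% and 73.8% it gives for 25 per arm. With 43 randomized it gives at most about 37% and 67%, and about 30% and 56% if 80% of them are retained.

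These figures rest on equal loss in the two arms, a near-equal split of the 43, and no gain from baseline adjustment. That gain could be anywhere from negligible to enough to close the gap at 20 per arm, and the article does not allow it to be fixed. *At least* is therefore unsupported rather than disproved. The conservative sentence is inconsistent with the article's own citations.

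The practical weight is modest. The trial is described as a pilot for estimating effect sizes, significance is not expected, and neither the feasibility nor the acceptability criterion depends on power.

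**What to change.** Keep the prospective calculation at 25 per arm and qualify it:

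1. Delete *at least*, and state that 43% and 75% assume 25 men per arm with complete follow-up in an unadjusted comparison.
2. Add the power at the 80% retention threshold: 20 per arm, about 35% for d = 0.51 and 64% for d = 0.75.
3. Note separately, as a matter of conduct, that 43 randomized gives at most about 37% and 67% on the same calculation.
4. If baseline adjustment is to be relied on, state the assumed correlation and the ratio of baseline to follow-up SD.
5. Delete the conservative sentence, or correct its citation and give the higher effect size.

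The cost is a few sentences and slightly less favourable figures. No change to the design or the analysis is needed.

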#### Planned Analyses

The primary aim of this study is to determine the feasibility, acceptability, and preliminary efficacy of the tailored PA intervention. We will consider the intervention feasible if at least 80% of the randomized participants are retained at the 6-month follow-up. The intervention will be considered acceptable if at least 80% of participants completing the 6-month follow-up respond favorably (*satisfied* or *very satisfied*) to the question *In general how satisfied were you with the intervention?* on the 6-month follow-up survey. We also asked more questions about intervention and study acceptability on the 6-month survey and the poststudy qualitative interviews described earlier. The main efficacy outcome was minutes per week of total MVPA, as measured by accelerometer data and PAR self-report, assessed at baseline and 6 months after baseline. The hypothesis is that participants in the PA intervention condition will have greater increases in minutes of total MVPA from baseline to post intervention (6 months) than participants in the control condition.

As a preliminary step, we will assess potential between-group differences in baseline characteristics (demographics and baseline PA level) using graphical methods and nonparametric and parametric tests as appropriate (eg, the Wilcoxon rank sum test for skewed data, *t* tests for normally distributed continuous data, and chi-square tests for categorical data). Any variables not balanced by randomization will be controlled for as covariates in subsequent analyses if they are correlated with the outcome (eg, minutes per week of MVPA) at a modest *P*<.10 level. We will estimate the preliminary efficacy of intervention compared with control using a generalized linear model in which we regress minutes per week of objectively measured MVPA at 6 months on the treatment assigned, baseline value of the outcome, and potential confounders (including those variables not balanced by randomization). To avoid the effects of outliers, we apply a normalizing transformation (if necessary) to the outcome before analysis. Should this transformation not adequately bring the data toward normality, we will model the median outcome (instead of the mean) using a quantile regression model.

Modeling is performed using a likelihood or quasi-likelihood–based approach and, thus, makes use of all available data (intent-to-treat sample) to produce consistent estimates of the regression parameters. Our goal is to estimate effect sizes, rather than strict statistical hypothesis tests. A similar modeling strategy will be used to estimate effects on self-reported minutes per week of MVPA.

Potential moderators will be examined using a similar analytic approach to that described earlier. For example, the total PA at 6-month follow-up (as measured by the accelerometer) will be regressed simultaneously on each moderator (eg, neighborhood PA environment profiles), as determined by latent class analysis, treatment assignment, and the interaction between the 2. If the interaction term is nonzero, we will conclude that there is evidence for a potential moderator. Models will also control for potential confounders of the association, including baseline PA and any variables unbalanced between arms. Our interest is in estimating effect sizes for conditional effects rather than strict statistical hypothesis testing.

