#### Visit 2 (PA Assessment and Randomization Session)

In-person participants returned for a second visit approximately 8 days after the first visit. They brought the accelerometer and the wear-time log form to the visit. Any participant with insufficient wear time (<3000 min over 4 days or <5 days of 600 min each) was asked to rewear the accelerometer, and the visit was rescheduled. Participants with sufficient wear time completed a 10-min treadmill walk to demonstrate moderate-intensity PA (3-4 miles per hour). Heart rate and rate of perceived exertion were documented throughout the treadmill walk by the study staff. The goal of the walk was to help improve the accuracy of participants’ self-report of their PA by providing a real-time demonstration of a 10-min bout of moderate-intensity PA with no breaks. The protocol for this demonstration was developed by [name] and has been used in earlier studies [11-13,64]. Participants then completed a 7-day PAR [62,63]. If participants reported more than 60 min of total MVPA in bouts lasting 10 min or more, they became ineligible.

Participants were then randomized to 1 of the 2 Spanish language internet and text message–based conditions: tailored PA intervention arm or nutrition and wellness control arm. Group assignment was determined using a permuted block randomization procedure with small randomly sized blocks. Randomization was stratified by the TTM stage of change [42,43] to ensure an equal distribution of treatment assigned across levels of motivational readiness for PA.

At the end of visit 2, the study staff helped participants in the tailored PA intervention arm to set up their personalized website account. The study staff also set up a bookmark to the page on the participant’s smartphone to aid easy access to the website and then provided thorough instructions on using all sections of the website. In the final phase of the visit, the study staff helped the participants set a personalized exercise goal and create a detailed PA plan for their first week. The staff members and the participants discussed potential barriers to completing this goal and how to overcome those barriers. The staff members walked the participants through these goal-setting steps and how to record their minutes of MVPA and goal on the website to ensure that the participants were able to complete these steps independently throughout the 6-month intervention.

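### The efficacy model does not commit to the stratification factor, stage of change, and its other covariates are chosen by baseline imbalance and correlation with the 6-month outcome

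*Protocol article*

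**What the plan says.** **Randomization.** Under Visit 2 (PA Assessment and Randomization Session) the Protocol article states: "Group assignment was determined using a permuted block randomization procedure with small randomly sized blocks". It continues "Randomization was stratified by the TTM stage of change", and gives the reason: "to ensure an equal distribution of treatment assigned across levels of motivational readiness for PA".

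**Baseline screening.** Planned Analyses begins: "we will assess potential between-group differences in baseline characteristics (demographics and baseline PA level) using graphical methods and nonparametric and parametric tests". Stage of change is not among the variables listed there.

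**Covariate rule.** The next sentence reads "Any variables not balanced by randomization will be controlled for as covariates in subsequent analyses if they are correlated with the outcome", with the correlation judged "at a modest *P*<.10 level".

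**Efficacy model.** Accelerometer MVPA at 6 months is regressed "on the treatment assigned, baseline value of the outcome, and potential confounders (including those variables not balanced by randomization"). Self-reported MVPA from the 7-day PAR is to be handled by a similar strategy. The moderator models adjust for baseline PA and any variables unbalanced between the arms.

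**Stage of change elsewhere in the analysis.** The Discussion (Importance of the Study) names baseline stage among the individual-level factors to be explored as moderators. No sentence places it in the efficacy model.

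**The concern.** The design singles out one baseline factor as important enough to stratify on, and the analysis then does not commit to using it. Stratified blocks reduce the chance variation of the treatment estimate only to the extent that the stratifier predicts the outcome. A model that omits a predictive stratifier leaves its variance in the residual and reports a standard error larger than the estimate's real variability. Intervals are then too wide and tests conservative. This matters because the article's stated goal is effect-size estimation, and the Power Analysis section says the data will size a future RCT.

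The second issue is timing. A rule that depends on correlation with the 6-month outcome cannot be applied until outcomes are in hand. Because the outcome differs between accelerometer and PAR, the rule can return different covariates for the two measures. The final model for at most 43 men therefore depends on which chance imbalances and correlations turn up.

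**Working it through.** **1. The plan's own figure.** The article gives no number for covariate choice. Its power statement is the nearest reference and it reproduces.
- Effect sizes: (42.5 − 9.0)/√((81.8² + 45.7²)/2) = 0.506, and (76.4 − 15.0)/√((113.5² + 22.6²)/2) = 0.750.
- Power with 25 per arm, Φ(d√(25/2) − 1.96): d = 0.51 gives Φ(−0.157) = 43.8%; d = 0.75 gives Φ(0.692) = 75.5%. The noncentral t gives 42.4% and 73.8%. The article states 43% and 75%.

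**2. How a variable gets into the model, from the text.**
- Baseline value of the outcome: always in.
- Demographics: in if unbalanced and correlated with the outcome at P<.10 (covariate-rule sentence), or if unbalanced alone (model sentence and moderator paragraph). These conditions differ.
- Stage of change: not in the screened list, balanced by design, and reachable only through the open term for potential confounders.

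**3. Cost of omitting stage, first simulation.** Assumptions: 40 men, 3 stage strata, stage effect 0.3 or 0.5 SD per step; 4,000 trials.
- 0.3 SD per step: SE 0.295 without stage and 0.286 with it; 0.295/0.286 = 1.03. Type I error without stage 4.45%.
- 0.5 SD per step: SE 0.310 and 0.286; 0.310/0.286 = 1.08. Type I error without stage 3.78%.
- Adding stage restores about 5%.

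**4. Second simulation, with the plan's rule applied.** Inputs from the article: n = 43 and stratified permuted blocks. Assumptions: block sizes 2 or 4, three strata, baseline-outcome correlation 0.4, six candidate covariates (two prognostic, coefficient 0.3), imbalance declared at P<.05, mean difference 0.51 SD for power; 4,000 trials per setting. SE and SD are from the null runs.

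| Stage-outcome correlation r | Model | Type I error | Power | Mean model SE | SD of estimate |
|---|---|---|---|---|---|
| 0 | no stage, no selection | 5.2% | 42.6% | 0.281 | 0.280 |
| 0 | plan's rule | 4.5% | 41.3% | 0.281 | 0.274 |
| 0 | stage added, no selection | 5.2% | 42.5% | 0.282 | 0.282 |
| 0.3 | no stage, no selection | 4.1% | 41.4% | 0.282 | 0.270 |
| 0.3 | plan's rule | 3.6% | 40.4% | 0.283 | 0.262 |
| 0.3 | stage added, no selection | 5.0% | 45.4% | 0.267 | 0.269 |
| 0.5 | no stage, no selection | 2.4% | 40.4% | 0.283 | 0.249 |
| 0.5 | plan's rule | 1.9% | 38.7% | 0.283 | 0.240 |
| 0.5 | stage added, no selection | 4.9% | 55.5% | 0.237 | 0.244 |

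Simulation error is about √(0.05 × 0.95/4000) = 0.3 points on type I error.

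**5. Check by formula.** In the second simulation the residual variance is 1 − 0.4² = 0.84 without stage and 0.84 − r² with it. The SE ratio is √(0.84/(0.84 − r²)): √(0.84/0.75) = 1.06 at r = 0.3 and √(0.84/0.59) = 1.19 at r = 0.5. The table gives 0.283/0.267 = 1.06 and 0.283/0.237 = 1.19. One stage step here is r√1.5, that is 0.37 or 0.61 SD. These are stronger links than in step 3, which is why the gap is larger.

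**6. The selection step.** In a separate screening simulation type I error was 4.5-4.7%, so selection did not inflate it. For a variable unrelated to the outcome, if imbalance is judged at 5% (the article sets no threshold), both conditions are met with probability about 0.05 × 0.10 = 0.005. For 13 independent variables (11 demographic items, the acculturation scale, baseline PA), 1 − 0.995¹³ = 6%.

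**The case against.** The strongest reply is that the text does not shut stage out. A reader might infer that only unbalanced variables can enter and that the rule excludes stage. The wording does not support that: the baseline value enters unconditionally, and the confounder set is open-ended. This part of the reply stands. What remains is that nothing commits the analyst to stage, and that the article states a selection rule explicitly, so this is not just a detail left to an analysis plan that is not shown.

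Second, the article gives no figure for how well stage predicts 6-month MVPA once baseline MVPA is in the model. Entry is limited to men reporting at most 60 minutes a week, which may narrow the spread of stages. This also stands. The size is conditional and vanishes if stage is not prognostic. In favour of some link, the article stratifies on stage, builds the tailored manuals on it, and cites the stage measure's concurrent validity with current activity levels.

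Third, this is a pilot that does not expect significance, and any error is conservative. That limits the severity. It does not remove the point, because the estimate and its precision are what the pilot passes on to the next trial.

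A reader might also infer that testing about a dozen baseline variables makes a spurious covariate likely. That ignores the correlation condition: step 6 gives about 6%, under an assumed threshold and independence.

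**Conclusion.** The point holds in a limited form. The article randomizes within stage of change but does not commit to analysing by it. Its remaining covariates are settled after outcomes are seen, under a rule stated inconsistently.

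If stage is prognostic beyond baseline MVPA, model-based standard errors without it are about 3-8% too wide for assumed effects of 0.3-0.5 SD per step, with type I error of 4.5-3.8% and some loss of power. At an assumed stage-outcome correlation of 0.5 the loss is larger (power 39% under the rule against 56% with stage added). At zero it is negligible. These figures come from linear models and do not carry over directly to the median-regression fallback.

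A reader might infer a biased treatment effect or an inflated false-positive rate. Neither follows: omitting a balanced factor does not bias the estimate, and no simulated setting showed the plan's rule taking type I error above 5%. The harm is miscalibrated precision and a model that is not fixed and may differ between accelerometer and PAR. The change is worth making, but the trial does not stand or fall on it.

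**What to change.** State one efficacy model: 6-month MVPA on arm, baseline MVPA and stage of change, with sparse stages merged by a rule written down in advance. Use the same covariate set for PAR, with baseline PAR as its baseline value. Remove the baseline significance tests and the P<.10 selection, and describe baseline characteristics by arm instead. Reword the model sentence and the moderator paragraph to match, so that one rule governs.

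The argument covers the stratification factor only. It does not support adding in-person versus distance participation, which was not a stratification factor.

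The Results section says cleaning and analysis are ongoing, so the change should be dated, with a note of whether outcomes by arm had been seen. The cost is wording plus about 2-3 degrees of freedom. With all 43 men, residual degrees of freedom go from 43 − 3 = 40 to 38 or 37.
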